### 3.3 Baseline Characteristics

Summaries will be provided to describe the subject populations in this study by study arm. Only subjects with data will be included in the summaries, i.e. missing data will be counted as missing.

We will report baseline characteristics in two ways:

- 1) Data on infants and children who are aged 6 weeks to 2 years residing in the service areas on November 1, 2008 (April 1, 2009)
- 2) Data on infants who are part of the Overall cohort of those who turn 6 weeks of age over the course of the entire study period, or who in-migrated at an age less than 24 weeks

Also by age groups: 6 weeks to 1 year, 1 to 2 years. Also by sex. Also, the proportions of children aged 12-23 months within each randomization unit with 1, 2, and 3 OPV doses. Also, by SES quintile...

### 3.4 Case Definitions and Severity Score

#### 3.4.1

- Seeking care for treatment of diarrhea at a treatment facility in Matlab, Nayargaon or Kalibazar.
- Age less than 2 years of age.
- Diarrhoea: three or more looser than normal stools in a 24 hour period.
- Acute rotavirus diarrhoea: an acute diarrhoeal illness episode in which rotavirus is identified in a stool sample collected as soon as possible but no later than 7 days after admission to the medical facility.
- Fever: rectal temperature  $\geq 38^{\circ}\text{C}$

Severe rotavirus Diarrhea:

Defined as a case of acute rotavirus diarrhea, as above, with a Vesikari score of 11 or greater; next most important will be for 15 greater.

Vesikari score (slightly modified for lack of full follow up of cases):

The completion of the diary card for each GE episode will allow the assessment of the intensity by using a 20-point scale. In this system, points will be assigned according to duration and intensity of diarrhoea and vomiting, the intensity of fever, presence of dehydration or

hospitalisation for each episode of GE as shown below:

| Sign/Symptom                                                 |                 | Points |
|--------------------------------------------------------------|-----------------|--------|
| Duration of looser than normal stools (days)          |                 |        |
| 1-4                                                          |                 | 1      |
| 5                                                            |                 | 2      |
| ≥ 6                                                          |                 | 3      |
| Maximum number of looser than normal stools /24 hours |                 |        |
| 1-3                                                          |                 | 1      |
| 4-5                                                          |                 | 2      |
| ≥ 6                                                          |                 | 3      |
| Duration of vomiting (days)                           |                 |        |
| 1                                                            |                 | 1      |
| 2                                                            |                 | 2      |
| ≥ 3                                                          |                 | 3      |
| Maximum number of episodes of vomiting/24 hours       |                 |        |
| 1                                                            |                 | 1      |
| 2-4                                                          |                 | 2      |
| ≥ 5                                                          |                 | 3      |
| Fever*                                                |                 |        |
| Rectally                                              | Axillary |        |
| 37.1 – 38.4°C                                                | 36.6 – 37.9°C   | 1      |
| 38.5 – 38.9°C                                                | 38.0 – 38.4°C   | 2      |
| ≥ 39°C                                                       | ≥ 38.5°C        | 3      |
| Dehydration**                                         |                 |        |
| 1-5%                                                         |                 | 2      |
| ≥ 6%                                                         |                 | 3      |
| Treatment                                             |                 |        |
| Rehydration                                                  |                 | 1      |
| Hospitalisation                                              |                 | 2      |

\* The highest temperature recorded during the episode will be scored.

\*\* Dehydration will be assessed clinically based on World Health Organisation criteria.

### *Adverse Events and Serious Adverse Events*

Overall mortality in the two types of study areas will be compared with Kaplan-Meier curves among those in the Overall population, up to earliest of: out-migration, 24 months of age, Mar 31, 2010. Statistical inference will proceed via Cox models with gamma frailty.

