Vaccination with Rotarix and surveillance activities for trial purposes will continue from study initiation through March 31, 2011. Surveillance for rotavirus gastroenteritis among children less than 2 years of age will occur at Matlab Diarrhoeal Hospital and the two community treatment centres of the Matlab HDSS continuously throughout the study period. Diarrheal illness information collected through surveillance will be linked to Rotarix study-specific data using the subject's HDSS identification numbers. The primary study endpoint will be the occurrence of an illness episode of acute diarrhoea, among infants and children presenting to a diarrhea treatment centre, determined to be caused by wild-type rotavirus found in a stool specimen. At the end of the surveillance period, rates of this primary study endpoint among age-eligible infants will be compared for villages randomized to receive Rotarix versus for villages randomized not to receive Rotarix. We expect that the rates of rotavirus diarrhoea will be significantly lower among children from the vaccinated villages. "Age-eligible" children is the cohort of children whose birthdate indicates that they could have received rotavirus vaccine if they resided in the villages assigned to vaccine, regardless of whether they actually received it (e.g. an intention to treat analysis comparing rates of rotavirus diarrhea among the cohort of children who were eligible to receive vaccine compared to age eligible children in the comparison villages who did not receive vaccine.)

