|                                                                         | 
Primary analysis
 
Those included: Infants who are residents in a Matlab village on the date upon which they turn 6 weeks (42 days) of age between Apr 1, 2009 (for ICDDR,B service area villages) or Nov 1, 2008 (for government service area villages) and March 31, 2011. In-migrant infants will be included if they in-migrate to a Matlab village when they are between 6 weeks and 20 weeks of age between Apr 1, 2009 (ICDDR,B service area) or Nov 1, 2008 (Govt service area) and Mar 31, 2011.
 
Follow-up period: Person-time will be counted from 6 weeks of age or age of in-migration until two years (731 days) of age or March 31, 2011, whichever comes first.
 
Secondary analysis
 
Those included: Identical to those in the “overall effectiveness-primary analysis” population plus those infants residing in study area villages who are between 6 and 20 weeks of age on Apr 1, 2009 (ICDDR,B service area) or on Nov 1, 2008 (Govt service area). Inclusion will then be restricted to those who received OPV1 (exclusive of birth dose) in a Matlab village after Apr 1, 2009 (ICDDR,B service area) or Nov 1, 2008 (Govt service area).
 
Follow-up period: Person-time will be counted from the date of OPV1 (exclusive of birthdose) until two years (731 days) of age or March 31, 2011, whichever comes first.
 |

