### *Primary Aim*

*To evaluate the population (overall) (Halloran, et al., 1997) effectiveness of Rotarix in reducing rates of acute diarrhoea due to rotavirus, as detected by patients admitted to a study treatment facility, among all infants and young children from villages where Rotarix is introduced compared to among those from villages where Rotarix is not introduced.*

Main analysis, on Overall population: first episodes of rotavirus diarrhea. A Poisson regression with Pearson scale parameter (calculated at the village level) will be fit, offset with person-years of exposure, with a dummy covariate for village randomization arm status and a dummy covariate for villages in the Matlab service area (corresponding to the stratified randomization).

Note that this overall effectiveness is a function of vaccine efficacy and vaccine coverage. Since over 90% coverage is expected, this will not be much different from a total effects analysis. Also, if there are any indirect effects that act to reduce transmission, these may exert a differential effect over time, as it is not until near the end of the study period that the entire population of children under 2 years of age will be saturated with vaccine.

Additional analysis: same as main analysis, but including **all** episodes of rotavirus diarrhea, not just first episodes. The scale parameter at the randomization unit level also accounts for all within-child correlation, so the same analysis approach can be used.

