### *Secondary Aims*

*1. To evaluate the total effectiveness of Rotarix in reducing rates of acute diarrhoea due to rotavirus, as detected by patients admitted to a study treatment facility, among vaccinated infants and young children from villages where Rotarix is introduced compared to unvaccinated infants and young children from villages where Rotarix is not introduced.*

Main analysis, “overall effectiveness” primary analysis population: with the modification of starting observation time at 12 weeks instead of 6 weeks of age. A Poisson regression with Pearson scale parameter (calculated at the village level) will be fit, offset with person-years of exposure, with a dummy covariate for village randomization arm status and a dummy covariate for villages in the Matlab service area.

Additional analyses:

- a. As in 1., but for all (not just first) cases of rotavirus diarrhea.
- b. As in 1. and 1.a, but for the mITT population.

*2. To evaluate the indirect effectiveness of Rotarix in reducing rates of acute diarrhoea due to rotavirus, as detected by patients admitted to a study treatment facility, among unvaccinated*

*infants and young children from villages where Rotarix is introduced compared to those from villages where Rotarix is not introduced.*

*Analyses are given according to the populations a, b, c given above.*

a) Those aged at least 20 weeks as of Nov 1, 2008 (Apr 1, 2009), with censoring at earliest of 2 years of age or Mar 31, 2001, whichever comes first. Also included are those who in-migrate between ages 20 weeks-2 years. Poisson regression as described above will be used; all cases (first and subsequent) will be used.

b) Those in the Overall population, but with censoring at first OPV dose. Because of the high coverage, this will not comprise many person-years. Poisson regression as described above will be used; all cases (first and subsequent) will be used.

c) All person-time contributed by infants or children who were between 6 weeks and 2 years of age at some point during the study period.

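### The mortality comparison stops on Mar 31, 2010, a year before follow-up of the same population ends; a second end date reads 2001, and most follow-up rules leave out death and out-migration

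*SAP*

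**What the plan says.** - **Mortality** (SAP, Adverse Events and Serious Adverse Events, within Section 3.4). Deaths in the Overall population are compared by Kaplan-Meier curves and gamma-frailty Cox models, with follow-up "up to earliest of: out-migration, 24 months of age, Mar 31, 2010". The contrast is described as being between the two types of study area.
- **Study period** (Section 2.1). "Vaccination with Rotarix and surveillance activities for trial purposes will continue from study initiation through March 31, 2011".
- **Overall population, primary analysis** (Section 3.2). Infants enter when they reach 6 weeks of age "between Apr 1, 2009 (for ICDDR,B service area villages) or Nov 1, 2008 (for government service area villages) and March 31, 2011". The follow-up rule is "Person-time will be counted from 6 weeks of age or age of in-migration until two years (731 days) of age or March 31, 2011", and the earlier of these two end points applies. The overall secondary, total and direct rules, and that for Indirect Population 1, end time at the same two points.
- **Indirect analysis a)** (Section 3.5, Secondary Aim 2). The population corresponds to Indirect Population 1 in Section 3.2, but is analysed "with censoring at earliest of 2 years of age or Mar 31, 2001, whichever comes first".
- **Primary model** (Section 3.5, Primary Aim). "Main analysis, on Overall population: first episodes of rotavirus diarrhea", by Poisson regression with a person-years offset. The migration rule at the start of Section 3.5 deals with moves inside the study areas, not with leaving them.

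**The concern.** An analyst who applies the mortality sentence as printed leaves out the last year of a study that runs for about two years in one area and about two and a half in the other. That year holds most of the person-time, because enrolment is continuous and follow-up accumulates late. Nothing else is planned under the safety heading. The SAP says in its Introduction that it exists to prevent data dredging and may be given to journal editors. A wrong date left in it means the true cut-off is settled after the data are in.

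The year 2001 in indirect analysis a) is the same kind of fault, since it falls before the study began.

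The follow-up rules raise a smaller question. The mortality sentence censors the Overall population at out-migration, but the effectiveness rules for that population do not mention it, nor death, nor (where only first episodes count) the first episode. Person-time after any of these is time in which a child cannot become a counted case.

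**Working it through.** The SAP states no person-time, death count or power for mortality, so there is no figure of its own to reproduce on that point.

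**1. Can the 24-month limit apply under the 2010 date?** Entry is at 42 days of age or later, and the limit is 731 days.

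| Earliest entrant | Age on Mar 31, 2010 | Age on Mar 31, 2011 |
|---|---|---|
| Government area, 6 weeks old on Nov 1, 2008 | 42 + 515 = 557 days | 42 + 880 = 922 days |
| ICDDR,B area, 6 weeks old on Apr 1, 2009 | 42 + 364 = 406 days | 42 + 729 = 771 days |

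An infant aged 20 weeks (140 days) on Nov 1, 2008 would be 140 + 515 = 655 days old on Mar 31, 2010. Under 2010 nobody reaches 731 days. Under 2011 the first entrants in both areas do.

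**2. Person-time kept.** Assume one entry per day at 6 weeks of age. With *d* days from opening to cut-off, an infant entering on day *t* contributes min(689, *d* − *t*) days, where 689 = 731 − 42. The sum is *d*(*d* + 1)/2 when *d* ≤ 689, and (*d* − 688) × 689 + 688 × 689/2 otherwise.

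| Area | To Mar 31, 2010 | To Mar 31, 2011 | Kept |
|---|---|---|---|
| Government | 515 × 516/2 = 132,870 | 192 × 689 + 237,016 = 369,304 | 36% |
| ICDDR,B | 364 × 365/2 = 66,430 | 41 × 689 + 237,016 = 265,265 | 25% |

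The SAP does not give the split of births between areas. If the government area supplies 40% of daily entries, the share kept is (0.4 × 132,870 + 0.6 × 66,430)/(0.4 × 369,304 + 0.6 × 265,265) = 30.3%. At 60% it is 32.4%. So about 68-70% is lost.

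**3. Children kept.** Entry days are 516 of 881 (59%) in the government area and 365 of 730 (50%) in the ICDDR,B area. Combined over the same 40-60% range this is 53.8-55.5%, so about 44-46% of children never enter.

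**4. Not stopping at the first episode.** Inputs from Section 2.5.1: 3.5% attack rate in unvaccinated villages, 50% effectiveness. With a constant hazard, the control hazard is −ln(1 − 0.035) = 0.03563, and 0.03563/0.035 − 1 = 1.8% excess person-time. The vaccine-arm hazard is half of that, giving a cumulative incidence of 1 − exp(−0.01781) = 1.766%. The ratio with uncensored denominators is 1.766/3.5 = 0.504, so effectiveness reads 49.6% instead of 50%.

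**5. Not stopping at death or out-migration.** The SAP gives no exit rates, so these are assumptions. With yearly exit rate *m* over one year, person-time is overstated by *m*/(1 − exp(−*m*)) − 1, which is 1.0% at *m* = 2% and 7.7% at *m* = 15%. Equal rates in the two arms cancel in the rate ratio. If the arms differ, a true ratio of 0.50 is multiplied by g(vaccine)/g(control), with g(*m*) = (1 − exp(−*m*))/*m*. Here g(0.05) = 0.9754 and g(0.10) = 0.9516. The ratio becomes 0.512 with 5% in vaccine and 10% in control villages, and 0.488 the other way round.

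**6. Yardstick.** At the planned 268 events and 50% effectiveness, about 89.3 cases fall in vaccine villages and 178.7 in the others. With the SAP's design effect, the standard error of the log rate ratio is √[3.48 × (1/89.3 + 1/178.7)] = 0.24, and the 95% interval for effectiveness is about 20% to 69%.

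**The case against.** The best defence is that both dates are evident slips. March 2011 appears in Section 2.1, Section 2.5 and nearly every follow-up rule in Section 3.2. The 24-month limit signals the error from inside the mortality sentence, and Section 3.2 gives the right date for the population in indirect analysis a). That is probably so, but the mortality sentence is the operative rule for that analysis and nothing else in the SAP overrides it.

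Four stronger readings are tempting, and the document does not support them.

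- *The effectiveness analyses are told to keep counting after death, departure or a first episode.* No sentence says so. The rules omit these ends, and an offset described as person-years of exposure could well be meant as time at risk. The omission also does not fit every population. Indirect Population 2 additionally stops at OPV1, Indirect Population 3 uses all person-time contributed, and the all-episodes analyses rightly continue after a first episode.
- *The primary estimate is materially biased.* A shift of 0.4 points is invisible in an interval from about 20% to 69%. Villages were randomised within each area, and nothing in the SAP suggests that exits differ by arm.
- *Mortality is compared between service areas instead of arms.* The wording allows that reading, but the check analysis in Section 3.6 uses similar wording for a contrast that makes sense only between Rotarix and non-Rotarix villages. It is ambiguous, not shown to be wrong.
- *About 70% of deaths are lost.* That figure is person-time. Survival analyses draw their information from deaths. If these cluster soon after entry, the loss moves towards the 44-46% of children who never enter.

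**Conclusion.** The mortality cut-off is wrong as printed and must be corrected. Taken literally it discards about 68-70% of the Overall population's person-time and about 44-46% of its children. These figures assume uniform entry at 6 weeks, a government-area share of 40-60%, and no allowance for in-migration or exits. The share of deaths lost cannot be derived from the SAP and may be nearer 45%. The 2001 date is a second slip, already contradicted by Section 3.2.

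The missing ends of person-time are a lesser matter of specification. They would lower absolute rates somewhat (about 1-8% over a year under assumed exits of 2-15%) but barely move the primary estimate. Even an assumed 5% versus 10% yearly loss shifts a rate ratio of 0.50 only to 0.488 or 0.512. The SAP's sample size is unaffected.

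**What to change.** 1. In the mortality paragraph, change the cut-off to March 31, 2011 and name the contrast as Rotarix versus non-Rotarix villages.
2. In Section 3.5, Secondary Aim 2, analysis a), change 2001 to 2011.
3. In Section 3.2, for the overall, total and direct populations and Indirect Population 1, end person-time at the earliest of death, out-migration from the study area, 731 days of age or March 31, 2011. In first-episode analyses only, also end it at the first rotavirus episode.

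The cost is wording. Dates of death and out-migration are already needed for the mortality analysis, so no new data are required.

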## 3.5 Statistical Analyses

Here we describe the analyses according to the study aims (in italics) listed in the protocol;

Vaccine population effectiveness parameters (with 95% CI) will be calculated as  $[1 - (\text{incidence rate of rotavirus among vaccine villages} / \text{incidence rate among the villages without vaccine})] \times 100$ .

For all analyses, we will handle migration of infants among study villages as follows: Regardless of the analysis, an infant or child's village of residence will be the one in which he or she first

enters the Overall population. This village assignment will be used regardless of migration within any of the study areas.

### *Primary Aim*

*To evaluate the population (overall) (Halloran, et al., 1997) effectiveness of Rotarix in reducing rates of acute diarrhoea due to rotavirus, as detected by patients admitted to a study treatment facility, among all infants and young children from villages where Rotarix is introduced compared to among those from villages where Rotarix is not introduced.*

Main analysis, on Overall population: first episodes of rotavirus diarrhea. A Poisson regression with Pearson scale parameter (calculated at the village level) will be fit, offset with person-years of exposure, with a dummy covariate for village randomization arm status and a dummy covariate for villages in the Matlab service area (corresponding to the stratified randomization).

Note that this overall effectiveness is a function of vaccine efficacy and vaccine coverage. Since over 90% coverage is expected, this will not be much different from a total effects analysis. Also, if there are any indirect effects that act to reduce transmission, these may exert a differential effect over time, as it is not until near the end of the study period that the entire population of children under 2 years of age will be saturated with vaccine.

Additional analysis: same as main analysis, but including **all** episodes of rotavirus diarrhea, not just first episodes. The scale parameter at the randomization unit level also accounts for all within-child correlation, so the same analysis approach can be used.

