## 2.2 Randomization and Blinding

There are 75 villages in the government comparison area and 67 villages in the intervention area. The villages in each area will be randomized separately. Infants in half of the villages in each area will be eligible to receive Rotarix during their EPI doses. In each area, villages will be randomly selected for Rotarix introduction after pre-stratifying on village size and baseline hospitalization rates/numbers for diarrhoea at the Matlab Diarrhoeal Hospital and community treatment centres during 2005 and 2006. Hospital charts for diarrhoea admissions will be reviewed to determine the number/rates of hospitalizations from those villages. The villages will be arranged sequentially based on diarrhoea admission number/rates to the Matlab and Nayergaon and Kalirbazaar treatment centres. For each stratum of villages, half of the villages will be randomly selected for introduction of Rotarix and the other half will for no introduction of Rotarix.

Although not a blinded evaluation, the introduction of bias will be reduced in several ways. First, the vaccine teams located in the EPI centres that are completely separate from the clinical settings where clinicians will be conducting surveillance. Second, the clinicians who treat the children when they present to a treatment facility are separated from those staff who carry out the vaccinations or conduct the laboratory testing. Third, the illness episodes are widely separated in

time from the vaccination, and thus the illness episode is not easily associated with receipt of vaccine. Fourth, laboratory assays for rotavirus will be carried out in the laboratory in Dhaka using coded specimens and are not conducted at the time of illness (since they have little clinical value). Although a parent could inform the clinician as to his/her child's participation in the study, this is believed to be an unlikely or important source of bias.

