## 2.5 Sample Size Considerations

### 2.5.1 Sample size calculations

The primary study endpoint will be admission for rotavirus gastroenteritis (see definitions, section 2.3.8). From 2003 to 2006 the average annual rotavirus admission rate to the Matlab Diarrhoeal Hospital among infants 0 to 11 months of age from the government comparison area was about 18.5 per 1000 and among infants 12 to 23 months of age it was 12.3 per 1000 (Table 3a); among infants 0 to 11 months of age from the intervention area it was 37.3 per 1000 and among infants 12 to 23 months of age it was 24.5 per 1000 (Table 3b). Because we will conduct surveillance among age-eligible infants continuously from study initiation, infants enrolled early will fall under longer surveillance while infants enrolled later will fall under brief surveillance (for example, only a few months). Additionally, because enrolment and surveillance for rotavirus diarrhoea will occur in the government comparison area and intervention area along different timelines, we used modeling to estimate a total study-period rotavirus diarrhoea hospitalization rate of 33 per 1000 infants (3.3%) (data not shown). With inclusion of infants admitted for rotavirus gastroenteritis at the Nayergaon and Kalirbazaar Community Treatment Centres, this rate may be slightly higher at 3.5%.

Because this is a cluster-randomized design, we must account for the intracluster (intra-village) correlation of acute rotavirus gastroenteritis. At the time of study planning, this value is not available for the study population. However, given the ubiquitous nature of rotavirus, we expected this value to be low (we assumed 0.02). Additionally, because we predefine clusters as villages for this study, we cannot set the cluster sizes to be equal; villages from the government comparison and intervention areas vary substantially in size (numbers of annual births). According to the timelines for enrolment for the 142 villages in from each area, the average cluster size is expected to be 65 with a coefficient of variation of cluster sizes is 0.96. Factoring in these values, along with the assumed intracluster correlation coefficient, into the calculation of the design effect for a cluster-randomized trial (Eldridge, 2006), we calculate a design effect of 3.48. Later estimations of the design effect based on rotavirus admission data for Matlab hospital place the design effect in the range of 2.9 to 4.5.

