#### **Sample size for the immunogenicity subset**

We assume that the seropositive rate of the immunized children with Rotarix would be 60% and for the non immunized children be 35%. A sample size of 90 in each group would allow

detection of this difference with an alpha of 0.05, two-sided, and 90% power. Assuming a 10% loss to follow up, 100 subjects in each group are needed to meet the required sample size

**Table 6: Total sample size estimates to detect a reduction in population incidence of rotavirus diarrhoea hospitalizations for different population effectiveness and baseline incidence rate assumptions, different design effect (DE) values and different numbers of required endpoints (type II error of 5%, 2-sided and 80% power).**

| DE=3.48     | Vaccine Effectiveness       |           |           |          |
|-------------|-----------------------------|-----------|-----------|----------|
|             | 50%                         | 60%       | 70%       | 80%      |
| Incidence*  | Required number of outcomes |           |           |          |
|             | 268 cases                   | 164 cases | 104 cases | 59 cases |
| 4.00        | 8937                        | 5846      | 4016      | 2464     |
| 3.75        | 9528                        | 6229      | 4287      | 2631     |
| 3.50 | 10210                | 6675      | 4594      | 2819     |
| 3.25        | 10997                       | 7190      | 4942      | 3035     |
| 3.00        | 11909                       | 7788      | 5352      | 3285     |

\*RV admission rate per 100 children

(Assumes 1:1 randomization. Half of these totals sample sizes may receive Rotarix.)

During the planned course of the study (through March 2011), it is estimated that a total of approximately 11,650 infants will be born into both groups (5825 per group, section 2.3.3). While this estimated total study population is higher than that required to achieve 80% power (10,210), if population effectiveness or the underlying attack rate of were lower than 50% or 3.5%, respectively, the study would quickly become underpowered. Because of these uncertainties we plan to continue enrollment and follow-up through March 2011 (which is practically to the end of the “winter” rotavirus season) in order to assure the study will have sufficient power.

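### Under the SAP's own planning assumptions, the Pearson-scaled Poisson model for the primary aim understates the standard error and gives about 10–12% type I error instead of 5%

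*SAP*

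**What the plan says.** SAP section 3.5, Primary Aim: "A Poisson regression with Pearson scale parameter (calculated at the village level) will be fit, offset with person-years of exposure". The covariates are randomization arm and service area. The same model serves the all-episodes analysis, total effectiveness (secondary aim 1) and indirect effectiveness in populations (a) and (b) (secondary aim 2). Secondary aims 4 and 5 repeat analyses for severe and all-cause diarrhoea. The SAP notes that the scale parameter also absorbs within-child correlation, but says nothing about unequal village size. It names frailty terms or robust variances only for Cox models.

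SAP section 2.5.1: "the average cluster size is expected to be 65 with a coefficient of variation of cluster sizes is 0.96". On the intracluster correlation (ICC): "we expected this value to be low (we assumed 0.02". The result: "we calculate a design effect of 3.48". It adds: "Later estimations of the design effect based on rotavirus admission data for Matlab hospital place the design effect in the range of 2.9 to 4.5".

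SAP section 2.2: "There are 75 villages in the government comparison area and 67 villages in the intervention area". Each area is randomized separately after "pre-stratifying on village size and baseline hospitalization rates/numbers for diarrhoea".

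The heading of Table 6 reads "type II error of 5%, 2-sided and 80% power". The 5% there is evidently the type I error.

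**The concern.** A Pearson scale assumes the same overdispersion in every village. With one common ICC, as in section 2.5.1, overdispersion grows with village size. The scale counts each village about equally, whereas the variance of the rate ratio is driven by the large villages. The analysis therefore leaves out the size-variation part of the design effect, although the sample size was raised from 77 to 268 events to cover all of it.

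At stake are the primary confidence interval and the claim that 0% effectiveness has been excluded. Both would look more precise than the data allow.

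**Working it through.** **Inputs.** From SAP section 2.5.1: mean village size m = 65, coefficient of variation CV = 0.96, ICC ρ = 0.02, control attack rate 3.5%, effectiveness 50%. From section 2.2: 75 + 67 = 142 villages.

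**1. Reproduce the plan's figures.**
- Design effect: 1 + ((CV² + 1)m − 1)ρ = 1 + (1.9216 × 65 − 1) × 0.02 = 3.478, the stated 3.48.
- Events: 77 × 3.48 = 267.96, so 268.
- Infants: 268 / (0.035 × 0.75) = 10,210.

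The sample-size figures are internally correct.

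**2. What the Pearson scale estimates.** Village i, of size mᵢ, has variance-to-mean ratio of about 1 + (mᵢ − 1)ρ. The scale is the sum of (observed − fitted)²/fitted over villages, divided by 142 − 3. It is close to an unweighted average, so it targets 1 + (65 − 1) × 0.02 = 2.28.

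**3. What the rate ratio needs.** In the variance of an arm's log rate, each village is weighted by its size. The weighted average of 1 + (mᵢ − 1)ρ is the formula in step 1, giving 3.48.

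**4. Consequence.** SE ratio = √(scale / design effect) and type I error = 2(1 − Φ(1.96 × SE ratio)). The first row uses the planning ICC. For the SAP's later range, ρ is solved from the design effect, taking that range to mean the size-weighted quantity in step 1.

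| Design effect | ρ | Pearson scale | SE ratio | Type I error, formula | Type I error, simulated |
|---|---|---|---|---|---|
| 3.48 | 0.0200 | 2.28 | 0.810 | 11.3% | 9.6–11.4% |
| 2.9 | 0.0153 | 1.98 | 0.827 | 10.5% | 10.0–11.3% |
| 4.5 | 0.0283 | 2.81 | 0.790 | 12.2% | 11.6–12.6% |

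The simulations used 142 villages, gamma or lognormal sizes, gamma village effects, no vaccine effect and the SAP's own model. At ρ = 0.02 with gamma sizes, the mean scale was 2.21 and the mean model SE 0.167, against an empirical SD of 0.208. An unscaled Poisson model gave 28%, so the Pearson scale removes much of the problem but not all of it.

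The 11,650 births expected in section 2.5 give 11,650 / 142 = 82 infants per village. The design effect is then 1 + (1.9216 × 82 − 1) × 0.02 = 4.13, the scale 1 + 81 × 0.02 = 2.62, the SE ratio 0.796 and the type I error 11.9%. Simulations gave 11.0–11.9%.

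**5. Is size variation the cause?** At ρ = 0.02, equal village sizes gave 5.3–5.9%, and CV 0.5 gave 7.1%.

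**6. Sensitivity to assumptions the SAP does not settle (simulated type I error).**
- ICC 0.01: 8.7–9.6%. ICC 0.005: 8.3%.
- Allocation in blocks of four by size and baseline rate, with assumed baseline-to-study correlations of 0 / 0.3 / 0.5 / 0.7: 11.2% / 10.5% / 9.5% / 8.5%.
- Between-village variation falling as 1/√size: 7.8–8.3%. Falling as 1/size: 5.7–6.2%.
- Event rate at one half / one fifth / one tenth, with the same relative village variation: 9.2% / 7.4% / 6.1%.

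**The case against.** The strongest reply is that the ICC is unknown. Section 2.5.1 says no value was available and treats 0.02 as a planning assumption. The result also needs the ICC to be equal in small and large villages, which the design-effect formula uses but the SAP never asserts as fact. A reader might infer that a CV of 0.96 alone guarantees the inflation. It does not: if the ICC fell as 1/size, the planned model would be close to nominal. That part of the objection stands. But such an ICC contradicts the constant value behind 3.48, and the SAP offers no reason to plan on one assumption and analyse on the other.

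Second, the trial stratifies on village size and baseline diarrhoea rates, and leaving those strata out of the model makes its SE conservative. This also stands in part: it lowers the error to about 8.5–10.5% for correlations of 0.3 to 0.7, but not to 5%.

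Third, a reader might infer that every secondary analysis suffers equally. It does not. Inflation fades as events per village become few. The SAP itself expects little person-time in indirect population (b), and Vesikari 15 or greater is necessarily rarer than the primary endpoint. The Cox analyses for indirect population (c) and direct effectiveness do not use the Pearson scale.

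Finally, the method is prespecified, works at village level and does not ignore clustering, and the point estimate is unaffected. That is true, but the interval and the test remain wrong under the plan's own assumptions.

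**Conclusion.** The concern holds as an inconsistency between planning and analysis. Section 2.5.1 allows for a variance inflation of 3.48, while the section 3.5 model would apply about 2.2–2.3 under the same assumptions. Two-sided type I error is then about 10–12%, and 95% intervals cover about 89–90%. This rests on an ICC that does not shrink with village size and on a CV near 0.96. With an ICC of 0.01, or with stratification that predicts study rates, the error is roughly 8–10%.

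Errors of 13–14% might be inferred, but the documents do not support them: across the SAP's range of 2.9 to 4.5 the highest simulated value was 12.6%. The finding covers the primary analysis and the secondary Poisson analyses with many events per village. It does not call the sample size or the effectiveness estimate into question.

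**What to change.** In all Poisson analyses of section 3.5, keep the model, offset, covariates and point estimate. Replace the Pearson-scaled variance by a village-clustered sandwich variance with a small-sample (leverage) correction and a t reference. Report the Pearson-scaled result as a sensitivity analysis. Section 1 says the plan is being finalized without knowledge of arm-specific results, so the change can still be prespecified.

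At ρ = 0.02 the HC3 form of this correction gave 4.8–5.6% type I error. It is not perfect: with lognormal sizes and a design effect of 4.5 it gave 6.4%. A negative binomial model also came close to nominal (5.2–5.5% at ρ = 0.02), but it reweights the villages and so changes the point estimate. It is not a like-for-like replacement.

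The cost is wording and a software option. Intervals become about 20–25% wider (√(3.48/2.28) = 1.235). Simulated power at 50% effectiveness falls from 92.9% to 87.6% with 142 × 65 = 9,230 infants, assuming the same relative between-village variation in both arms. If 3.48 applied in both arms, as in the sample-size calculation, a correct variance would give the roughly 80% power for which 268 events were chosen.
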